## Abstract

**Background:**

This study tests whether home visitation to prevent child maltreatment can be improved by adding manualized program components, targeting four key risk factors for child maltreatment: low parental self-efficacy, high levels of perceived stress, parental anger, and post-traumatic stress symptoms. Home visitation is widely implemented, but effects on child maltreatment risk tend to be modest at best. Home visitation tends to be rather flexible (i.e., professionals decide how to support each family). We will test whether adding manualized program components increases program effectiveness, by ensuring that key risk factors are addressed, while maintaining flexibility. In addition, we will test whether any component effects on reduced child maltreatment risk can be explained (i.e., is mediated) by ameliorated risk factors. Lastly, we will test whether the components are more effective for some mothers (e.g., those at highest child maltreatment risk) than for others.

**Methods:**

We will conduct a randomized controlled trial among 398 mothers enrolled in a Dutch home visiting program targeting families at risk for child maltreatment. Mothers in the experimental group will receive the manualized components in two consecutive home visits, while mothers in the control group will receive regular home visits (care as usual). Mothers will fill out questionnaires at four time points: before and after each of the two home visits. Outcome variables include the four targeted risk factors parental self-efficacy, perceived stress, parental anger, and (recognition of) post-traumatic stress symptoms, as well as parenting practices (e.g., rejection and affection), and risk for child maltreatment.

**Discussion:**

This study aims to determine whether adding manualized program components to a flexible home visiting program increases program effectiveness on risk for child maltreatment. In addition, our test of whether the effects of the components on risk for child maltreatment is explained (i.e., mediated) by amelioration of the targeted risk factors, may contribute to our understanding of the role of these risk factors in child maltreatment. Our tests of which mothers benefit most from adding the components may help move the field towards evidence-based personalized family support.

**Trial registration:**

This trial has been retrospectively registered in the Netherlands Trial Register (NL8005).

## Background

Child maltreatment comes with serious long-lasting consequences for its victims, including physical and mental health problems, and poor academic and employment outcomes [1–5]. Home visiting programs are among the most widely implemented programs for the prevention of child maltreatment [6, 7]. Yet, these programs tend to yield only modest effects on reduced risk for child maltreatment, on average around Cohen’s *d* = 0.24–0.29 [8–10]. This means that of one hundred families receiving home visitation, only seven to nine actually benefit more from such programs than from care as usual [11]. Although it is common for prevention programs to yield relatively small effects [10, 12], because only a subset of the families will develop towards child maltreatment, these numbers highlight the need to increase the effectiveness of home visiting programs to prevent child maltreatment.

On average, home visiting programs are less manualized than other parenting programs (e.g., parenting group programs) [13]. As such, they allow for flexibility – professionals can decide how to support each family, based on clinical experience and perceived individual family needs [14]. Many scholars argue for this flexible approach [15, 16]. Other scholars, however, argue for manualized programs, based on scientific evidence of effective ways to address key risk factors to increase the likelihood of program effectiveness [17, 18]. Although these standpoints may seem incompatible, manualizing a program does not necessarily have to compromise the flexibility that professionals have in delivering the program [19]. Adding a limited set of manualized components that target key risk factors to flexible, largely non-manualized home visitation, may increase program effectiveness, by ensuring that certain key risk factors are targeted in all families, while allowing professionals to maintain flexibility. For example, professionals can still decide, based on clinical experience and individual family needs, how to organize their sessions (e.g., the content of what they discuss with parents). Indeed, home visiting programs that ensure that specific program content is delivered, for example using fidelity checks, tend to yield larger effects than home visiting programs that do not use such checks [20]. In this experimental study, we will test whether adding manualized components that target four key risk factors increases the effectiveness of a home visiting program to ameliorate these risk factors, and to reduce risk for child maltreatment.

### Risk factors targeted in the current study

We selected four dynamic (i.e., malleable) key risk factors for child maltreatment to explicitly target in a home visiting program to prevent child maltreatment: compromised feelings of parental self-efficacy, high levels of perceived stress, parental anger, and post-traumatic stress symptoms [21–23]. First, lower parental self-efficacy, i.e., the belief to be less able to perform the parenting role successfully and to have less control over a child’s behavior and development, may limit mothers’ ability to persist in parenting practices that take more effort [24, 25]. Mothers who feel less self-efficacious tend to be less warm towards their children and use less positive and sensitive parenting practices [26, 27]. Instead, they are more inclined to engage in harsh and inconsistent parenting practices [27, 28]. Therefore, increasing parental self-efficacy may support mothers in sensitive parenting, reducing the risk for child maltreatment. Meta-analytic data support this hypothesis, by showing that child maltreatment prevention programs that include components to increase parental self-efficacy tend to be more effective in reducing mothers’ risk for child maltreatment than programs without such a component [10].

Second, mothers who perceive high levels of stress experience more mental health problems [29, 30], which can lead to engagement in more intrusive, punitive and harsh parenting practices [31–33]. Increasing mothers’ skills to cope with stress, might help them to relieve their stress, giving them more mental space to adopt positive parenting practices in challenging situations and reducing their risk for child maltreatment. Indeed, a meta-analysis shows that child maltreatment prevention programs that explicitly include components to enhance personal skills (e.g., stress management skills) tend to be more effective in reducing mothers’ risk for child maltreatment than programs without such a component [10].

Third, mothers who have difficulty regulating their anger are more inclined than other mothers to express their anger in ways that are harmful for their children [29, 34]. Anger regulation difficulties may be caused by both the extent to which mothers experience feelings of anger, and the extent to which they express their anger in harmful ways [35]. Feelings of anger in mothers at risk for child maltreatment are often intensified by mothers’ dysfunctional attributions about their child’s behavior [36]. For example, mothers might believe that their child’s challenging behavior is intended to upset or annoy them, which may intensify their feelings of anger. Strong feelings of anger can then make them resort to harmful ways of expressing their anger [36]. Thus, altering parents’ dysfunctional attributions and supporting them to express their anger in non-harmful ways, may help to reduce risk for child maltreatment. Indeed, adding a program component focused on dysfunctional attributions and anger management to a parent group training reduced risk for child maltreatment at termination of the program and reduced long-term dysfunctional attributions [37]. This could also apply to home visiting programs.

Last, mothers at risk for child maltreatment tend to have experienced more traumatic events than the general population, increasing their risk for post-traumatic stress symptoms (e.g., emotional numbness and increased arousal) [38, 39]. These symptoms may hamper mothers’ emotional availability to their children and may make it difficult for mothers to be aware of their own emotions until they are so strong that they resort to harsh and punitive behavior [40, 41], increasing the risk for neglect and aggression [42, 43]. In addition, post-traumatic stress symptoms may interfere with intervention effects and increase the risk for drop-out [38, 39, 44–46] . Adequate recognition of these symptoms and referral by home visitors to professional help may therefore reduce mothers’ risk for child maltreatment [40].

In this study, we test whether manualized components designed to target these four key risk factors for child maltreatment ameliorate these risk factors and whether they improve parenting practices and reduce risk for child maltreatment. To further improve our understanding of the role of these four risk factors in the reduction of risk for child maltreatment (i.e., our theory of change), we will also test whether amelioration of these risk factors explains (i.e., mediates) the effects of the components on reduced risk for child maltreatment.

### Potential differential effects

Not all mothers may benefit equally from these components. On the one hand, mothers who are at highest risk considering the targeted risk factors may benefit more as they have the largest room for improvement [47, 48]. On the other hand, mothers who are at lower risk may benefit more, as they may be more able to engage with program content [49]. Other aspects may also influence the degree to which mothers benefit from the components, such as children’s temperament. For mothers whose child is often frustrated or hard to soothe, it may be more difficult to apply newly learned behaviors (e.g., stay calm when their child upsets them) [50]. However, these mothers may be in greater need for strategies to deal with this child behavior, and thus benefit more from components that target their stress and anger regulation [51]. Furthermore, the accumulation of life events (e.g., quitting one’s job or death of a family member) may either hinder mothers to benefit from the components, if it makes mothers less able to engage with program content [52], or may increase the effectiveness of the components, if they buffer the adverse effects of accumulation of life events [53]. In this study, we will therefore examine maternal (initial levels of targeted risk factors), child (temperament), and family (life events) characteristics as putative moderators of the effects of the manualized components on the targeted risk factors and on risk for child maltreatment. Knowledge on differential effects of the added components can serve to guide personalization of programs. In other words, it can support home visiting programs in their goal to serve individual family needs in an evidence based way.

### Study aims

In this study, we will test (1) whether manualized components designed to target four key risk factors for child maltreatment (low parental self-efficacy, stress, parental anger, and post-traumatic stress symptoms) indeed ameliorate these risk factors; (2) whether adding these manualized components to a home visiting program improves parenting practices and reduces the risk for child maltreatment; (3) whether any effect of the manualized components on reduced risk for child maltreatment can be explained (i.e., is mediated) by amelioration of the four targeted risk factors; (4) whether some mothers benefit more from the manualized components than other mothers in terms of ameliorated risk factors and reduced risk of child maltreatment.

## Methods/design

### Design

We will conduct a randomized controlled trial in the context of an existing Dutch home visiting program aimed at the prevention of child maltreatment (Supportive Parenting, in Dutch “*Stevig Ouderschap*” [54]). Mothers will be randomly assigned to receive either two consecutive home visits that include the additional manualized components (i.e., manualized home visiting), or to receive standard home visits (i.e., care as usual) with a 1:1 allocation using a computerized random number generator.

### Participants

Participants will be *N* = 398 mothers enrolled in the Supportive Parenting program. The program is part of care as usual in many municipalities in the Netherlands. Approximately 51% of all Dutch newborns live in a municipality that offers Supportive Parenting. Their parents receive a screening questionnaire in the first week after giving birth (the Instrument for early identification of Parents At Risk for child Abuse and Neglect; IPARAN [49]). Approximately 6.5% of families show an elevated risk on child maltreatment based on this instrument, for example, due to a history of child maltreatment, or a lack of social support in either one or both of the parents. These families are offered Supportive Parenting. Supportive Parenting targets both mothers and fathers. That said, mothers are mostly present during Supportive Parenting home visits [55] and we therefore focus specifically on mothers in this study.

### Intervention

The Supportive Parenting program consists of six 90 min home visits conducted by child health nurses within the first 18 months after birth. During these visits, nurses support parents by enhancing their parenting knowledge and skills and by strengthening their social support system. A large part of every home visit is flexible and parents can choose the topics they wish to discuss (for a more detailed description of the program, see [54, 56]). The nurses who deliver the program work in regional youth health care centers, similar to Well Baby clinics in the United States, and have followed a two-day training for delivering the Supportive Parenting program. A previous study among 469 mothers shows that mothers who received Supportive Parenting report more appropriate expectations of their children, less oppression of their child’s independence, and less worrisome child development compared to mothers receiving care as usual. Regarding risk for child maltreatment, findings were mixed. There was no mean difference in risk for child maltreatment, but a higher percentage of mothers who received Supportive Parenting showed a reliable reduction in risk for child maltreatment (22%), relative to mother receiving care as usual (8%) [57].

### Added Manualized components

We designed four manualized components targeting low parental self-efficacy, high levels of perceived stress, parental anger, and post-traumatic stress symptoms**.** Nurses will implement these components in two consecutive home visits for mothers in the experimental group.

#### Increasing parental self-efficacy

Nurses will give structured positive feedback about mothers’ parenting practices at least twice in both home visits. Nurses are free to choose which parenting practices they will target in their feedback, but the feedback is designed to tap into multiple sources of self-efficacy: mothers will have a sense of mastery, they will be verbally persuaded, and they will be compared positively to other mothers [24]. This component is based on the work of Mouton and Roskam [58], who showed that a similar systematic way of providing positive feedback to mothers increased parental self-efficacy and the use of positive parenting practices.

#### Reducing levels of perceived stress

Nurses will provide mothers with a 10-min guided imagery relaxation exercise, on audio, in which mothers are instructed to imagine a place where they feel safe, calm, and relaxed. The script used in the exercise is based on the work of Naparstek [59] and the Dartmouth Student Wellness Center [60]. We adapted the wording and some of the examples to suit mothers with low educational levels, using specific guidelines for Dutch texts [61], and the input of several nurses who work as home visitors for Supportive Parenting. Guided imagery relaxation exercises like these can positively affect both perceived stress and physiological stress in a range of populations (e.g., [23, 62, 63]). Listening to guided imagery exercises has also shown to decrease levels of anxiety and pain in hospital settings, for example prior to surgery [64]. Nurses will encourage mothers to listen to the exercise daily by playing the audio file during the home visit, explaining the positive effects it may have for their well-being, and helping mothers choose a time and place for the daily exercise.

#### Reducing parental anger

This module is designed to alter negative attributions that mothers might have about their child’s behavior and provide mothers with alternative strategies to respond to child behavior that triggers anger. To do this, nurses will discuss several ways to recognize anger and techniques to calm down when feeling angry. More specifically, nurses will discuss mothers’ anger triggers (i.e., child behavior that evokes anger in mother) and negative attributions (e.g., ‘my child tries to upset me’) using a set of cards, based on the work of Kock and colleagues [21]. Each card describes child behavior that may evoke anger in mothers, possible reasons for the child’s behavior and possible strategies to respond to such behavior.

#### Recognizing post-traumatic stress symptoms

Nurses will use the two-item version of the abbreviated Post Traumatic Stress Disorder Checklist – Civilian (abbreviated PCL-C [65]) to assess the level of mothers’ post-traumatic stress symptoms. This checklist is an adequate screening instrument for post-traumatic stress disorder (PTSD) with a sensitivity of .95 and a specificity of .50 in women [65]. Nurses will motivate mothers who score above the threshold, indicating that they might suffer from PTSD, to consult their general practitioner in order to receive therapy (e.g., eye movement desensitization and reprocessing therapy; EMDR [66, 67]).

### Procedure

Figure 1 shows an overview of the study procedure. Nurses will inform mothers enrolled in Supportive Parenting about the study purposes and invite them to participate. To support nurses in this, we will contact each of them monthly, by phone, email, or in person. Mothers interested in participating send their contact details to the research team, who will contact them to discuss the study procedures and to sign informed consent for study participation. See the Appendix for the consent form used in this study. Only after informed consent is obtained after explanation by the research team, participants will be allocated to either the experimental or the control group by the researchers, using a computerized random number generator. Participants are not blind to the conditions (they know whether they receive added components or not), but mothers are not aware of the study hypotheses.

**Fig. 1 Fig1:**
[figure not shown]
Participant flow chart

This study will follow mothers over the course of any two consecutive Supportive Parenting home visits, which will be named home visit A and B in this study. Home visits tend to be about three months apart from each other, but this may vary in clinical practice. Mothers will fill out online questionnaires four times; one to two weeks before home visit A visit (T1), one to two weeks after home visit A (T2), one to two weeks before home visit B (T3), and one to two weeks after home visit B (T4). We offer mothers assistance in filling out the questionnaires by phone. We will send text messages by phone to remind mothers to fill out the questionnaires. Mothers receive a compensation of 5 euros for each questionnaire they fill out, and an additional 5 euros if they fill out all the questionnaires.

Mothers in the experimental group will receive two Supportive Parenting home visits (A and B) in which nurses will deliver the manualized components. All four components will be delivered in both home visits. Mothers in the control group will receive two regular Supportive Parenting home visits that do not include the manualized components. As we do not expect any adverse effects from these components, we did not set any criteria to discontinue the components. There are no restrictions for mothers to seek any additional help, but mothers are asked to report it if they do so.

This study has been approved by the Ethics Review Board of the Faculty of Social and Behavioral Sciences of the University of Amsterdam (ref nr: 2018-CDE-9258) and the trial has been registered in the Dutch Trial Register (NL8005). Any meaningful changes will be reviewed by the Ethics Review Board of the Faculty of Social and Behavioral Sciences of the University of Amsterdam and will be reported in the effect paper.

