### Analyses

Prior to analyzing the data, missing data will be handled with multiple imputation. To test whether adding manualized components ameliorates four risk factors (i.e., low parental self-efficacy, high levels of perceived stress, parental anger, and post-traumatic stress symptoms), improves parenting practices, and reduces risk for child maltreatment, we will conduct multivariate analyses of covariance (MANCOVA) and an analysis of covariance (ANCOVA) respectively, with baseline scores (T1) as the covariates, with data of T2, T3, and T4 for the risk factors and data of T4 for parenting practices and risk for child maltreatment as dependent variables.

To test whether amelioration of the targeted risk factors by the added components explains (i.e., mediates) reduced risk for child maltreatment we will conduct a mediation analysis using the PROCESS Macro in SPSS [80]. This macro computes 95% confidence intervals of the indirect effects based on 1000 bootstrap samples. Intervals that do not include 0 indicate a mediation effect.

To test who benefits most from the manualized components we will test whether condition × child, maternal, or family characteristic interaction effects predict ameliorated risk factors and reduced risk for child maltreatment. Putative moderators include mothers’ baseline levels of each of the four risk factors (maternal characteristics), children’s temperament (child characteristic), and the number of life events in the past year and during the study (family characteristic).

We will conduct interim descriptive analyses for our progress annual reports for the study funder. However, no interim analyses that answer the research questions of this study will be conducted. The full protocol, anonymized dataset, and the statistical code that will be used in this study will be available upon motivated request after publication of the results in a peer-reviewed paper.

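### Entry at any two consecutive visits mixes child ages and programme stages, and the stated models cannot separate moderation by temperament from moderation by either

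*Protocol article*

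**What the plan says.** Intervention describes a programme of "six 90 min home visits conducted by child health nurses within the first 18 months after birth". Procedure adds: "This study will follow mothers over the course of any two consecutive Supportive Parenting home visits". On spacing it says: "Home visits tend to be about three months apart from each other, but this may vary in clinical practice". On who is approached it says: "Nurses will inform mothers enrolled in Supportive Parenting about the study purposes and invite them to participate". Neither Participants nor Procedure limits entry by child age or visit number, and Design describes 1:1 allocation with no stratification by either.

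In Analyses, the MANCOVA and ANCOVA are run "with baseline scores (T1) as the covariates". For aim 4, "we will test whether condition × child, maternal, or family characteristic interaction effects predict ameliorated risk factors and reduced risk for child maltreatment". The moderators named are the baseline levels of the four risk factors, child temperament and life events. Table 1 shows temperament measured once, at T1, and lists neither child age nor visit number.

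**The concern.** The entry rule lets in mothers at very different points. One may have a very young baby and little or no earlier contact with the programme. Another may have a child of a year or more and four visits behind her. Several outcomes (anger towards the child, harshness, play, feeling competent as a parent) plausibly change over that period. The effect of the components may change too. The anger component works with child behaviours that provoke anger and with the motives mothers read into them, and how well this fits may depend on the child's age. The self-efficacy component adds to a programme that already teaches parenting skills, so the number of earlier visits may matter.

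For aims 1 and 2, a baseline fact that may explain outcome variance is left in the error term.

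For aim 4 more is at stake. Temperament is not randomised, and its ratings may shift with age. If they do, a finding that mothers of hard-to-soothe children benefit more could reflect temperament, the child's age or the stage of the programme. The Discussion wants these results to help personalise family support, and the three explanations lead to different rules for whom to offer the components.

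**Working it through.** **Permitted spread at entry.** Inputs: six visits (Intervention); any two consecutive visits, about three months apart (Procedure).

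- Home visit A can be visit 1, 2, 3, 4 or 5.
- Spread in child age = (5 − 1) gaps × 3 months = 12 months. Earlier visits range from 0 to 4.
- T1 comes one to two weeks before home visit A and after consent. If this makes entry at visit 1 rare, the spread is (5 − 2) × 3 = 9 months, with 1 to 4 earlier visits.

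These are ranges the rule permits. The actual distribution of entry visits is not given.

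**The plan's own figure.** For d = .25, one-sided α = .05 and power .80, the normal approximation gives n per arm = 2 × (1.645 + 0.842)² / .25² ≈ 198, or 396 in total. With the t distribution, 199 per arm gives power .801 and 198 gives .799. N = 398 is reproduced, and nothing below changes it.

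**Aims 1 and 2: bias.** Child age and earlier visits are fixed before randomisation, so they are balanced in expectation. Assume entry is spread equally over visits 1 to 5:

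- SD of age at entry = 3 × √2 = 4.2 months.
- SE of the difference in mean age between arms = 4.24 × √(2/199) = 0.43 months.
- 95% range of chance imbalance = ±1.96 × 0.425 = about ±0.8 months.

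That is small, and adjustment for T1 scores absorbs part of its influence.

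**Aims 1 and 2: precision.** Let R² be the share of residual variance that age would explain. The document gives no value, so a range is assumed. Power = Φ(.25 × √(199/2) / √(1 − R²) − 1.645). The equivalent number of extra mothers = 398/(1 − R²) − 398.

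| R² (assumed) | Power | Equivalent extra mothers |
|---|---|---|
| 0 | .80 | 0 |
| .02 | .81 | 8 |
| .05 | .82 | 21 |
| .10 | .84 | 44 |

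**Aim 4: what the temperament interaction estimates.** Suppose the condition effect changes by g SD per SD of child age and does not depend on temperament once age is held fixed. Suppose also that age and temperament score correlate r. A model with condition × temperament but without condition × age then gives a temperament interaction of r × g. Assumed values show the span:

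- r = .1, g = .1: .1 × .1 = .01 SD per SD of temperament.
- r = .3, g = .2: .3 × .2 = .06.
- r = .5, g = .3: .5 × .3 = .15.

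The span runs from negligible to more than half of the .25 SD effect the trial is sized for. Nothing in the document says where in it this trial lies. The algebra shows only that the coefficient mixes the two sources. The same holds with programme stage in place of age.

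**Price of separating them.** Adding condition × age widens the interval for condition × temperament by a factor of about 1/√(1 − r²): 1.005 at r = .1, 1.05 at r = .3, 1.15 at r = .5.

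**The case against.** The strongest reply has four parts.

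*Randomisation already protects the main comparison.* This stands. A reader might infer that the treatment effects for aims 1 and 2 are biased or confounded by child age. The document does not support that: allocation is individual and random, and T1 scores are adjusted for. An extra prognostic covariate is a matter of efficiency.

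*An interaction carried by age is still real.* This stands too. A reader might turn r × g into an inflated false-positive rate for the temperament test. If hard-to-soothe children are more often of an age at which the components work better, their mothers do benefit more in this population, and rejecting the null is not a type I error. Any such rate would also rest on correlations the document does not give. What is unclear is the explanation, and whether the result carries over to a service with a different mix of ages or stages.

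*The article is condensed.* This stands in part. The T1 covariates are stated for the MANCOVA and ANCOVA, no covariate list is given for the moderation models, and the moderator list is worded as open. A fuller plan might add age. But the models that are described contain neither age nor stage, and Table 1 does not show them being collected.

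*A year is the permitted maximum.* This stands, and is why the spread is given as up to about 9-12 months.

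**Conclusion.** The entry rule permits child age at T1 to differ by up to about 9-12 months and earlier exposure by up to four visits, and neither is among the stated covariates or named moderators.

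For aims 1 and 2 this causes no bias. It forgoes some precision of unknown size; the gain from power .80 to .81-.84 rests on an assumed R² of 2-10%.

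For aim 4, the condition × temperament interaction, as described, cannot be told apart from an interaction of condition with child age or with programme stage. This limits what the result can say about whom to offer the components. It does not show that the temperament test is invalid. How much it matters depends on how strongly temperament ratings follow age and how far the effect varies with age, and the document gives neither. The sample size is unaffected. The change is worth making before analysis, mainly for aim 4.

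**What to change.** 1. Record child age and the visit number of home visit A at T1. Record both, because spacing varies and one need not stand in for the other. Both are fixed before randomisation, so for mothers already enrolled they can be retrieved later without bias.
2. Add child age at T1 as a prespecified covariate in the MANCOVA and ANCOVA.
3. Fit condition × child age (or condition × visit number), with its main effect, beside condition × temperament, at least as a prespecified sensitivity analysis. Report the temperament interaction with and without it.

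The cost is one or two extra data items, one or two degrees of freedom, and a wider interval for the temperament interaction (about 5% if age and temperament correlate .3, about 15% if .5). Recruitment was ongoing when the article was written, so the items can still be added. The article does not say whether the research team already holds them, so some retrieval through the nurses may be needed.
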